### Theory

The X:IT II intervention is based on the theoretical framework of the X:IT study (the Theory of Triadic Influence) and is as such not applying specific new theories addressing social inequality in smoking. The results from the qualitative process evaluation of X:IT suggested that the practical application of the theoretical methods was inaccessible for children and parents from low SEP. The theoretical framework of the study is based on these findings and the fact that the X:IT interventions are population wide and meant to reach adolescents across socioeconomic positions.

### Evaluation

#### Design

The X:IT II intervention will be evaluated by means of effect in a difference-in-difference design. Hence, all participating schools will receive the same intervention, and students from high and low social classes will be compared in the difference-in-difference design [32]. Process evaluation will be conducted at specific time points during the intervention period. Data collections are shown in Table 2.

**Table 2 Tab2:** Data collection of the X:IT II study – timeline, instrument and source of data

	Baseline September 2018	Intervention	Follow-up 1 May 2018	Intervention	Follow-up 2 April 2019	Intervention	Follow-up 3 April 2020
Students	Questionnaires (students start year 7)		Questionnaires (students end year 7)	Observations and interviews	Questionnaires (students end year 8)		Questionnaires (students end year 9)
School coordinators	Questionnaires		Questionnaires		Questionnaires		Questionnaires
Teachers		Monthly questionnaires on curricular activities (September – June)		Observations and interviews Monthly questionnaires on curricular activities (September – June)		Monthly questionnaires on curricular activities (September – June)	

#### Recruitment plan and study population

The recruitment period ran from January 2017 till June 2017, the intervention started in September 2017 and runs until June 2020. The recruitment ended up having two steps. First, 300 schools were randomly selected and contacted by email and by postal letter, followed up by telephone calls. The aim of this first step was to recruit 156 schools, which could be randomly selected into an intervention and a control group, i.e. to conduct a randomized controlled trial.

However, after contacting each of the 300 schools by telephone, it became clear that this aim was too ambitious, as only 60 schools showed any interest to be included in the study. In the second step of the recruitment phase, we decided to include all interested schools as intervention schools. However, three of these schools were for children with special needs and were therefore excluded from the evaluation, leaving 57 schools. After the summer holiday, when the final commitment from schools were needed and the data collection was about to start, 11 of the schools withdrew from the evaluation; in two schools, there was a new school leader who did not prioritize the intervention; two schools had assigned to too many projects and had to prioritize; at the remaining seven schools lack of time was the primary reason for resigning. Therefore, baseline data included 46 schools from all over Denmark.

#### Power calculations

Power calculations were based on the following assumptions: Each school cluster includes on average 50 students, the intra class coefficient for current smoking among grade 9 students is 0.053, smoking prevalence of 17.9% in grade 9, an expected reduction in smoking of 25 to 13.4%, and a power of 80%. Power calculations were conducted according to Donner & Klar (1996) [33] and showed a need for 48 schools with approximately 2400 students.

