One of the limitations of this study is that we did not succeed in recruiting the required number of schools for a randomized design. The clustering of smoking in schools and classes leads to the need of a very high number of schools for an RCT, in this case 78 schools for intervention and 78 for comparison. The main purpose of the X:IT II study is to examine the differences between high and low SEP and the mechanisms behind these differences. The difference-in-difference design suits this purpose. There are two main assumptions to the difference-in-difference design, the assumption of parallel trends and the assumption of common shocks. First, the parallel trends assumption states that trends in outcomes between the exposed and comparison groups are parallel prior to the intervention. As we know from the literature, that smoking is more prevalent among both adolescents and adults from lower SEP [1, 43], it is not possible to fulfill this assumption. On the other hand, at the beginning of grade 7, very few students have become smokers and as such a trend in smoking is not calculable in this age group. We expect that the second assumption of common shocks stating that any events occurring during or after the intervention will equally affect the exposure and comparison groups, will be fulfilled. Power calculations for the difference-in-difference design showed a need for 48 schools, which was fulfilled in the recruitment where 57 schools gave consent to participate. However, as previously described only 46 schools participated in the baseline data collection.

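### The stated need for 48 schools at 80% power does not follow from its listed inputs, and those inputs do not describe the high-versus-low SEP contrast that will be analysed

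*Protocol article*

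**What the plan says.** The Power calculations section gives four numerical inputs besides the 80% power. The mean cluster size is 50 per school. On clustering it states that "the intra class coefficient for current smoking among grade 9 students is 0.053". The starting prevalence is 17.9%, and the effect is given as "an expected reduction in smoking of 25 to 13.4" percent. It names a published cluster sample-size method and concludes that the calculation "showed a need for 48 schools with approximately 2400 students". No alpha is listed.

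The Discussion gives the requirement for the randomised design first planned as "in this case 78 schools for intervention and 78 for comparison"; the recruitment section gives the same total, 156. It then says: "Power calculations for the difference-in-difference design showed a need for 48 schools, which was fulfilled in the recruitment", referring to the 57 schools that consented. The next sentence discloses that "only 46 schools participated in the baseline data collection".

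Under Design and under Data process and analyses, all schools receive the intervention. High-SEP students are the comparison group, low-SEP students are the exposed group, and a difference-in-difference of zero is stated to be the aim.

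**The concern.** Two things do not fit. First, one set of inputs sits beside two very different answers: 48 schools in total in one section and 156 in another. Only one of these can come from the listed figures. Second, the smaller number is assigned to a design that the inputs do not describe. One overall fall from 17.9% to 13.4% is an intervention-versus-control effect. A high-versus-low SEP difference in change needs the share of students in each SEP group, the prevalence in each, and a difference to detect or a margin to exclude.

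This matters more than usual because the hoped-for result is a null. An imprecise estimate near zero can be read as equal benefit across SEP groups, and a stated 80% power encourages that reading.

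**Working it through.** **Inputs.** From the Power calculations section: m = 50 per school, ICC = 0.053, p1 = 0.179, p2 = 0.134 (a 25% reduction is exactly 0.179 × 0.75 = 0.13425), power 80%. Assumed: two-sided alpha 0.05, so (1.960 + 0.842)² ≈ 7.849.

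**The plan's figure of 48.**
- The student number agrees with the school number: 48 × 50 = 2400.
- Design effect: 1 + (50 − 1) × 0.053 = 3.597.
- Unpooled variance: n per arm = 7.849 × (0.179 × 0.821 + 0.134 × 0.866) / 0.045² = 1019. Schools per arm = 1019 × 3.597 / 50 = 73.3.
- Pooled variance: n = 1023, giving 73.6 per arm; with p2 = 0.13425, n = 1035, giving 74.5.
- Pooled with continuity correction: n = 1067, giving 76.8 per arm; with p2 = 0.13425, n = 1079, and 1079 × 3.597 / 50 = 77.6, which rounds up to 78.

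The last variant reproduces the randomised-design figure of 78 per arm (156 in total) exactly. The figure of 48 is not reproduced.

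**Other routes to 48, keeping 80% power.**
- Two arms, one-sided alpha 0.05: 116 to 124 schools in total.
- One-sample test against 17.9%: 38 to 39 schools.
- Within-school comparison of two equal groups, no clustering inflation: 41 to 43 schools.
- Low-SEP share of about 30%, no clustering inflation: 47 to 50 schools. Neither the share nor the clustering assumption is stated.
- 25 students per SEP group per school: design effect 1 + 24 × 0.053 = 2.272. One group then needs 1023 × 2.272 = 2324 to 1079 × 2.272 = 2451 students. Taking one group's number as the total and dividing by 50 gives 46.5 to 49 schools; counting both groups gives 93 to 98.

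Numbers near 48 thus appear only under assumptions that the article does not state.

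**Power if 48 is read as a two-arm comparison of schools.**
- 24 per arm: effective n = 1200 / 3.597 = 333.6; SE = √(0.2630 / 333.6) = 0.0281; 0.045 / 0.0281 − 1.96 ≈ −0.36; power about 36%.
- 48 per arm: effective n = 2400 / 3.597 = 667.2; SE = 0.0199; power about 62%.

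**Illustrative precision for the SEP contrast with 46 schools.** Students: 46 × 50 = 2300. The Background gives prevalences at age 15 of 8% for higher SEP and up to 24% where parents receive welfare benefits. The low-SEP share is not given, so a range is assumed. The calculation allows for no attrition and no clustering inflation, and takes the simple difference in follow-up prevalence, without the baseline term.

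Half-width = 1.96 × √(0.24 × 0.76 / n_low + 0.08 × 0.92 / n_high)

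| Low-SEP share | n_low | n_high | 95% half-width (points) |
|---|---|---|---|
| 10% | 230 | 2070 | 5.6 |
| 20% | 460 | 1840 | 4.1 |
| 40% | 920 | 1380 | 3.1 |

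The whole hypothesised reduction is 17.9 − 13.4 = 4.5 points.

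**The case against.** The best defence is that X:IT II has no arms of whole schools. SEP groups are compared among students of the same schools, and the Setting section says that catchment areas almost always span a wide range of backgrounds. The full design effect of 3.597 need not apply to such a contrast. With equal SEP groups and no inflation, 17.9% versus 13.4% would need only 41 to 43 schools, fewer than the 46 available. This stands. It blocks two inferences that a reader might draw:

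- That 78 per arm is the true requirement for X:IT II. It is what the listed inputs give for a two-arm comparison of schools, and nothing shows that it applies to the SEP contrast.
- That the study has only about 36% power. That figure, like the 62%, assumes arms of whole schools. Power for the SEP contrast is undocumented, which is different from shown to be low.

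A reader might also take the Discussion to claim that 46 schools satisfy a need for 48. It does not: the word fulfilled refers to the 57 consenting schools, and the fall to 46 is disclosed at once. What remains is a disclosed shortfall of two schools (2300 against 2400 students) without restated power.

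Finally, an article may leave an attrition allowance to the full protocol, so its absence is not counted here. The same allowance does not rescue the 48: the article itself names the inputs, the result and the design to which the result is said to belong.

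**Conclusion.** The statement is wrong as written. At a two-sided alpha of 0.05, the listed inputs give about 73 to 78 schools per arm for a two-arm comparison, not 48 in total, and one-sided alpha 0.05 does not close the gap. The inputs also cannot support a power statement for the SEP difference-in-difference, because they contain nothing about SEP. The 80% power is therefore unsupported for the contrast that the Discussion calls the main purpose of the study.

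The illustrative half-widths of 3.1 to 5.6 points range from about two thirds of the hypothesised overall reduction (3.1 / 4.5 = 0.69) to more than all of it (5.6 / 4.5 = 1.24). An estimate near zero could therefore be compatible with a sizeable difference between SEP groups. These half-widths rest on an assumed SEP split, on the Background prevalences (the 24% being an upper value), and on no attrition or clustering inflation. They show the scale of the issue and are not an estimate of what the study will achieve.

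**What to change.** In the Power calculations section and the matching Discussion sentence, do one of two things:

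- give the inputs and formula that yield 48 for the SEP contrast: alpha and sidedness, SEP shares, SEP-specific prevalences, the difference or margin, and the clustering assumption; or
- withdraw the statement of 48 schools at 80% power.

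In either case, state the expected 95% half-width or the power that 46 schools give for the SEP difference-in-difference, using the observed SEP split and expected attrition. The 78 per arm should remain described as the randomised-design figure and not be presented as the requirement for this design.

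The cost is one rewritten paragraph and one Discussion sentence. No recruitment or design change is needed; the only drawback is that the stated power may become less favourable.

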#### Implementation

Implementation was launched by a one-day-kick off workshop for school coordinators and leaders in the beginning of the school year 2017/2018. Representatives from the municipalities were also invited. The program for the day was planned and presented by staff from the Danish Cancer Society who developed and revised the intervention and the teaching materials, as well as staff from the Centre for Intervention Research in charge of evaluating the intervention.

The kick-off workshop included a detailed presentation of the intervention materials, the aim and background for the study, results from the evaluation of X:IT, and the rationale for the X:IT II intervention and evaluation. There was also room for reflection and chatting in smaller groups about experiences and expectations about implementing the intervention components. A folder with all background information about the curricular activities and good advises for implementation was given to the participants.

Parents were informed about the study and their involvement by two means: 1) at meetings for parents at each school in the beginning of the school year, 2) as written information on the actual smoke free agreement that students brought home. Students were informed about the study by the school coordinator at the school, and they received written information designed specifically for them.

### Effect evaluation

The effect evaluation will be based on quantitative data from questionnaires answered by students and project coordinators at schools. We will measure smoking status, sociodemographic factors including socioeconomic position of the family, and covariates such as parental and friend’s smoking at baseline.

### Primary outcomes

Frequency of smokers at grade seven, eight and nine measured by student self-reported questionnaires.Degree of implementation after first, second and third year of intervention by student self-reported questionnaires and project coordinator questionnaires.

Measurements of the main variables are described in Table 3.

**Table 3 Tab3:** Main variables measured in the X:IT study

Variables	Source of data	Items	Response categories	Dichotomizations and coding
Frequency of student smoking	Student self-reports	“How often do you smoke at present?”	Every day; not every day, but every week; not every week, but every month; more seldom than every month; never	Smokers are defined by ever smoking vs. never
Socioeconomic position	Student self-reports	“Does your father (mother) have at job?”	Yes; no; don’t know; don’t have/see my father (mother)	Information is coded into categories 1 (high) to 5 (low) according to the standards of the Danish National Research Institute of Social Research. Categories 6 (unclassifiable) and 7 (economically inactive) are added.
		“Why doesn’t he (she) have a job?”	He (she) is: sick; a student; seeking work; retired; staying at home; don’t know	
				Family social class is coded at the highest ranking parent
Degree of implementation (Adherence, dose, quality of delivery, participant responsiveness)^a^	School coordinator reports	(Adherence): “Are pupils allowed to smoke during school hours?”	Yes; yes outside school grounds; no	Adherence to the rules for smoke free school time are fulfilled if the school coordinator responds “no”
	Student self-reports	(Dose): “How often do you see students smoke different places at school?”	Daily; sometimes; never	Dose are fulfilled if students report never seeing other students smoking at school

^a^All measures of implementation are described in detail in Bast et al. 2016

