**Methods:**

Main intervention components are smoke free schools, a curricular component, and parental involvement (smoke free agreements and talks about tobacco). Components have been revised from the first version; 1) previously, schools should be smoke free on the school ground and were encouraged to hide smoking so that it wasn’t visible to pupils from the school ground. Now they are encouraged to tighten the rules so that no pupils or teachers smoke during the school day, no matter where they are; 2) the specifically developed educational material (Up in Smoke) has been revised so that all materials are online and all texts has a ARI; 3) the parental involvement is now targeted multiple groups of parents, e.g. parents that are smokers, and parents of children that smoke. Language used is simpler and the website for parents presents very specific examples.

X:IT is implemented in 46 Danish public schools from fall 2017 until summer 2020. Data is collected through electronic questionnaires to students and coordinators four times (fall 2017, spring/summer 2018, 2019 and 2020). Further, qualitative interviews and observations are conducted.

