#### Intervention components

##### Smoke free school grounds (smoke free school time)

Compared to most countries in the Western world, Denmark has had a very lenient smoking policy. Cigarette prices are relatively low and the first law restricting smoking in public places was adopted in 2007. In August 2012 smoking was fully banned for students, employees and visitors at Danish school grounds. This law was passed during the period of the first evaluation of X:IT. Therefore, the smoke free school ground component was revised accordingly. In the X:IT II intervention, the rules for smoke free schools are even firmer than the national law; here schools are encouraged to secure that there is no smoking anywhere at the school ground, or outside the school ground, during school hours. In Denmark, this is known as ´Smoke free school time´. The smoke free school time applies for students as well as teachers, other employees and visitors. Previous studies showed that students exposed to teacher smoking during the school day were more susceptible to smoke themselves [26–28].

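### Table 3 scores adherence to smoke free school time from a pupil-only question, although the component also binds staff and visitors

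*Protocol article*

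**What the plan says.** The section on smoke free school grounds sets out the revised component. Smoking is to be absent on and outside the school ground during school hours, and "The smoke free school time applies for students as well as teachers, other employees and visitors". The Abstract (Methods) describes the same tightening, "so that no pupils or teachers smoke during the school day, no matter where they are". The component section supports the inclusion of adults with earlier evidence that "students exposed to teacher smoking during the school day were more susceptible to smoke themselves". It also notes that Danish law has banned smoking on school grounds for students, employees and visitors since August 2012.

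Under Primary outcomes, degree of implementation after each of the three years is the second listed primary outcome. Table 3 prints two items for it, both on this component:

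- Adherence, from the school coordinator: "Are pupils allowed to smoke during school hours", with the response options "Yes; yes outside school grounds; no". The coding is "Adherence to the rules for smoke free school time are fulfilled if the school coordinator responds" no.
- Dose, from the students: "Dose are fulfilled if students report never seeing other students smoking at school".

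A footnote to Table 3 sends the reader to a 2016 publication for all implementation measures. Process evaluation says that the assessment builds on measures developed in the first X:IT evaluation. Data collections says that enforcement of smoke free school time is asked of students and coordinators in every questionnaire, without giving the items.

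**The concern.** The variable is labelled as adherence to the rules of the component, but it records only whether the rule for pupils is in place. The part left out is part of what X:IT II adds. On-grounds smoking was already illegal for everyone, so the step beyond the law is the ban on smoking off the grounds during school hours. For pupils the item captures that step, because permission to smoke outside the grounds does not count as adherent. For adults it captures nothing, although the article gives exposure to teacher smoking as a reason for the component.

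Two results are at stake. The first is the reported level of adherence, which feeds a primary outcome. The second is the set of analyses announced in the Discussion that relate smoking to the implementation actually achieved. All participating schools receive the intervention, so differences in implementation are the only contrast in exposure between schools. The Background shows that such grading mattered in the first trial: the odds ratio for smoking uptake was 0.65 at medium and 0.44 at full implementation, with no significant effect at low implementation.

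**Working it through.** The article has no figure to reproduce here. The check sets the component definition against the Table 3 rule and then works out which way any error runs.

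**Step 1: definition against scoring.**

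| Smoking permitted in school hours | Breach of the component? | Effect on the Table 3 adherence score |
|---|---|---|
| Pupils, on the grounds | Yes | Coded not adherent |
| Pupils, off the grounds | Yes | Coded not adherent (second response option) |
| Teachers and other staff, off the grounds | Yes | None |
| Visitors, off the grounds | Yes | None |

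Smoking by adults on the grounds would also be a breach and also leaves the score unchanged, but it has been illegal since 2012. The practical gap is therefore adults off the grounds. The printed dose item concerns smoking by other students, so it cannot reveal this case either.

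**Step 2: direction.** A school where pupils may smoke breaches the component whatever its adults do, so a coding of not adherent is right. A school where pupils may not smoke is coded adherent whether or not adults may. If coordinators answer correctly, every miscoding turns a partly adherent school into an adherent one.

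**Step 3: effect on the reported level.** Let n be the number of the 46 baseline schools coded adherent, and m the number of those that still permit adult smoking. Assume that all 46 coordinators answer.

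- Reported adherence = n/46.
- Adherence as the component is defined = (n − m)/46.
- Overstatement = m/46, so each such school adds 1/46 = 2.2 percentage points.

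The article gives neither n nor m. All that follows is that m lies between 0 and n.

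**Step 4: effect on an adherent versus non-adherent contrast.** Let f = m/n. Let g say where the miscoded schools lie on the outcome: g = 0 if they resemble fully adherent schools, g = 1 if they resemble non-adherent ones. With mean outcomes A (adherent) and N (non-adherent), the group coded adherent has mean

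(1 − f)A + f[A + g(N − A)] = A + fg(N − A),

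and the observed contrast is (N − A)(1 − fg). It is unchanged if f or g is 0 and shrinks by the fraction f if g = 1. The article fixes neither f nor g, and it does not state that this two-group contrast is the analysis to be run.

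**The case against.** The strongest reply is that the Table 3 row is plainly an excerpt. It names four dimensions (adherence, dose, quality of delivery, participant responsiveness) but prints items for only two, and only for one of the three main components. The footnote points elsewhere for the full measures, Data collections mentions several enforcement questions to two sources, and Process evaluation adds fieldwork and interviews. An item on staff smoking may well exist, and a journal article need not print it.

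Much of this stands. A reader might infer that staff smoking goes unmeasured altogether, and the article does not support that. What the reply does not remove is the printed coding. Table 3 does not merely list the pupil question as an example. It says that adherence to the component's rules is met when that question is answered no. If a staff item exists, the rule as printed ignores it. Nor does it help that schools are only encouraged to adopt the policy, because the question is whether a school labelled adherent meets the rules so named.

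Three further points limit the concern, and all three stand:

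- A reader might infer that partly implementing schools are scored as fully implementing X:IT II. The rule scores one dimension of one component. Overall degree of implementation also draws on other dimensions and the other components.
- A reader might infer that the main comparison is biased. The Discussion gives the difference between high and low socioeconomic position as the main purpose. The estimator under Statistical methods compares changes in outcome between those groups without using the adherence score. Per-protocol analyses are announced there too, but nothing ties them to this score.
- A number of affected schools, or a percentage loss of contrast, would have to be assumed without any basis in the article. A large loss also requires that schools banning all pupil smoking behave like schools with no such ban, which need not be so.

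**Conclusion.** The point holds for the coding rule. Under Table 3 a school can be adherent to smoke free school time while permitting what the component excludes, namely smoking by staff or visitors off the grounds during school hours. Given accurate answers, adherence on this dimension can only be overstated, by 2.2 percentage points for each such school if all 46 report. The analyses by implementation may be diluted, by an amount between nothing and the share of adherent-coded schools that are miscoded, provided those schools lie between the two groups on the outcome. The article supports no narrower figure.

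The consequence is confined to the implementation outcome and the analyses that use it. The socioeconomic difference-in-difference estimate is not affected as stated. The correction is worth making because the variable feeds a primary outcome and the change is small.

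**What to change.** In the remaining follow-up coordinator questionnaires, ask the Table 3 question, with the same three response options, once for teachers and other employees and once for visitors. If such items are already among the enforcement questions mentioned under Data collections, use those. Change the coding line in Table 3 so that adherence to smoke free school time is met only when all answers are no.

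Keep the pupil-only score alongside it for comparison with the first X:IT. For any wave without the added items, report that score as adherence to the pupil smoking rule, not as adherence to the component.

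The cost is a slightly longer coordinator questionnaire, one changed coding line and an adherence figure that can only stay the same or become less favourable. Waves already collected without the items cannot be repaired and remain limited to the pupil-only score.
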